## Abstract

**Background:**

Resistance exercise is known to be effective in reducing glycated haemoglobin (HbA1c) in people with type 2 diabetes. However, studies, so far, have employed supervised resistance exercise in a laboratory or gym facility which limits the future translation of such exercise in to clinical practice and recommendations. Our primary aim, therefore, is to test the hypothesis, in a randomized controlled trial, that home-based resistance exercise training and gym-based resistance exercise training both reduce HbA1c levels in people with type 2 diabetes compared to control. We will also investigate the effects of home- and gym-based resistance exercise training on muscle strength and body composition.

**Methods:**

The current study is a three-arm randomised controlled trial which will be conducted with 150 eligible people with type 2 diabetes to compare home-and gym-based resistance exercise training with usual care in Kuwait. The interventions will be delivered by exercise specialists and last for 32 weeks. The primary outcomes are HbA1c with secondary outcomes measuring muscle function, body composition, physical activity and quality of life.

**Discussion:**

Ethical approval has been granted by the Dasman Diabetes Institute ethical review committee (RA/197/2019). Study findings will be disseminated through presentation at scientific conferences and in scientific journals.

**Trial registration:**

NCT04136730: Retrospectively registered on 21 October 2019

## Administrative information

Note: the numbers in curly brackets in this protocol refer to SPIRIT checklist item numbers. The order of the items has been modified to group similar items (see http://www.equator-network.org/reporting-guidelines/spirit-2013-statement-defining-standard-protocol-items-for-clinical-trials/).

## Introduction

### Background and rationale {6a}

The main role of muscle is to allow body movements via the generation of force, with the importance of this highlighted in conditions associated with muscle mass loss, such as sarcopenia [1]. Additionally, skeletal muscle has a critical, but often overlooked, role in metabolism [2]. For example, skeletal muscle is the primary protein store in the body, and during starvation [3] or conditions such as acquired immune deficiency syndrome (AIDS), can provide gluconeogenic precursors which are crucial for survival [4]. On top of this, as muscle is the primary site for glucose disposal in the body, it is therefore important in metabolic conditions such as diabetes [5]. Extending this further, the association of muscle in lifelong health is reflected by data demonstrating the association of muscle mass/function with mortality. This is highlighted by our recent work where we demonstrated, in ~ 500,000 participants (40–69 years) from the UK Biobank, that each 5 kg lower grip strength was associated with a higher risk of all-cause mortality [HR (95% CI) men 1.16 (1.15 to 1.17) and women 1.20 (1.17 to 1.23)] as well as a broad variety of other health outcomes [6]. Similarly, we have demonstrated that the increased risk of all-cause and CVD mortality in people with type 2 diabetes (T2D) is attenuated in those with high grip strength (CVD mortality with low [HR (95% CI) 4.05 (2.7 to 5.80)] vs high [HR 1.46 (0.87 to 2.46)], both relative to people without T2D with low grip strength) [7]. Taking this evidence together, this indicates that the maintenance of muscular mass and strength is of clear importance for public health.

Muscle strength is determined through a combination of multiple modifiable and non-modifiable factors. The primary modifiable factors are genetics with data indicating that hand grip strength is ~ 50% hereditable [8]. On the non-modifiable side, the primary factors important for the maintenance of muscle mass/strength are nutrition, particularly sufficient protein intake (e.g., [9]), and physical activity, particularly resistance exercise which is even effective in nonagenarians [10]. Resistance exercise has been shown, in a wide variety of populations, to be efficacious in increasing muscle mass and function, increasing basal metabolic rate, reducing blood pressure, improving blood lipids and glycaemic control [11]. Indeed, a meta-analysis in 2011 found that resistance exercise training can result in a 0.6% reduction in HbA1c in people with type 2 diabetes [12].

It is clear, therefore, that targeting increased muscle mass via resistance exercise may be effective in improving glycaemic control in people with type 2 diabetes, yet very few people participate in such exercise [13, 14]. One barrier to participation in resistance exercise is that access to equipment in specialised exercise facilities is required. This is a particular problem for resistance exercise, with aerobic exercise activities, such as walking/jogging, freely accessible to all without any training or expensive equipment. The majority of studies, which have demonstrated the efficacy of resistance exercise in reducing HbA1c, have been carried out in specialised exercise facilities/laboratories with each session supervised by a qualified instructor. There is the need, therefore, to develop a resistance exercise programme that is more accessible to the wider population. To date, little is known about the effectiveness or feasibility of home-based resistance training, without supervision, in people with type 2 diabetes.

### Objectives {7}

Our primary aim is to test the hypothesis, in a randomized controlled trial, that home-based resistance exercise training and gym-based resistance exercise training both reduce HbA1c levels in people with type 2 diabetes compared to control. We will also investigate the effects of home- and gym-based resistance exercise training on muscle strength and body composition.

### Trial design {8}

The current study is a three-arm randomised controlled trial comparing usual care plus home- or gym-based resistance exercise training interventions versus a usual care control group maintaining habitual physical activity levels. Eligible participants will be identified from clinics and via adverts places locally and on social media and we anticipate recruiting 150 participants with type 2 diabetes to the study. Baseline data will be measured prior to randomisation, and follow-up data will be collected 16 weeks and 32 weeks after randomisation adjusted for any delays in the start of the intervention post-randomisation.

## Methods: participants, interventions and outcomes

### Study setting {9}

This is a single-centre, DASMAN diabetes institute, three-arm randomised controlled trial.

### Eligibility criteria {10}

Potential participants will receive a mailed prestudy invite which will provide details on study information and details around eligibility. If still interested, potential participants will be invited to the research site where eligibility will be determined based on the inclusion and exclusion criteria (Table 1).

**Table 1 Tab1:** Inclusion and exclusion criteria

In order to be considered eligible for participation in the study they must:	
Criterion	Characteristic of eligible participants
1	Be male or female aged ≥ 21 years at time of consent
2	Have physician diagnosed type 2 diabetes (HbA1c of 48 mmol/mol or over)
3	Have had no changes in anti-diabetic medication in the last 3 months
4	Have a BMI < 5 kg m^−2^
5	Have a blood pressure < 160/100 mmHg
6	Not be receiving insulin therapy
7	No currently, or in the last year, be participating in any vigorous aerobic activity (> 1 h per week)—defined a activity requiring a large amount of effort which causes rapid breathing and a substantial increase in heart rate
8	Not currently be participating in any resistance exercise training
9	Be a Kuwaiti resident
10	Not have any other condition that prevents exercising safely

### Who will take informed consent? {26a}

Written consent will be obtained by a member of the study team during a visit to the research site for the baseline assessment, with no study procedures taking place until consent has been obtained. At the baseline visit, a member of the study team will confirm eligibility.

### Additional consent provisions for collection and use of participant data and biological specimens {26b}

Not applicable

## Interventions

### Explanation for the choice of comparators {6b}

Following the baseline assessment, patients will be randomised to the home- or gym-based resistance exercise group or the control group (1:1:1 ratio) using a computer generated randomisation sequence. Randomisation will be stratified by sex.

### Intervention description {11a}

#### Control

Patients in the control group will receive usual clinical care and will be instructed to maintain their normal dietary and physical activity habits.

#### Home-based resistance exercise

Participants assigned to the home-based resistance exercise group will be asked to perform exercises 3 times a week for the intervention period. Each session will begin with a 5-min warm-up and end with a 5-min cool-down, walking on the spot/stretching. Exercises will target all major muscle groups. The exercises will be press-ups, band lateral raises, band seated low row, squat, lunge, calf raise, and plank. The order of each session will be (1) squat, (2) press up, (3) calf raise, (4) band seated low row, (5) lunge, (6) band lateral raise and (7) plank. Where participants are unable to perform any of the exercises, suitable alternatives will be sought.

The first 3 sessions of the exercise will be performed, within our exercise facility, under the supervision of a qualified exercise specialist to ensure that the participants are comfortable with the exercises and are performing them appropriately. During these sessions, participants will perform 5–10 repetitions of each exercise (tiring but comfortably achievable). A similar session, within the gym facility, will take place at week 4 and then every 4 weeks of the study to overcome any issues with the exercises and to ensure progression to an appropriate intensity. In weeks 2–4, participants will perform, during each session, a single set of each exercise with this set performed to voluntary muscular failure—defined as not being able to perform another repetition. In weeks 5–8, this will progress to 2 sets of each exercise with both sets performed to voluntary muscular failure, in each session. In weeks 9–32, 3 sets of each exercise will be performed with all sets to voluntary muscular failure, in each session. When multiple sets (weeks 5 onwards) of each exercise are performed, these will be sequentially with 2 min rest between each set.

#### Gym-based resistance exercise

Participants assigned to the gym-based resistance exercise group will undertake 3 supervised sessions per week. Each session will begin with a 5-min warm-up and end with a 5-min cool-down, walking or cycling and stretching. The exercises performed during each session will consist of leg press, calf press, leg curl, chest press, lateral raise, seated row, and plank. The order of the session will be (1) leg press, (2) chest press, (3) calf press, (4) seated row, (5) leg curl, (6) lateral raise and (7) plank. Where participants are unable to perform any of the exercises, suitable alternatives will be sought.

Exercises will be performed at 65–80% one repetition maximum (1RM), and this will be re-tested every 4 weeks of the intervention and the load adjusted accordingly. In week 1, participants will perform, during each session, a single set of 5–10 repetitions of each exercise (tiring but comfortably achievable) to ensure they are comfortable with the exercises and are performing these in the correct form. In weeks 2–4, participants will perform, during each session, a single set of each exercise with this set performed to voluntary muscular failure—defined as not being able to perform single another repetition. In weeks 5–8, this will progress to 2 sets of each exercise with both sets performed to voluntary muscular failure, in each session. In weeks 9–32, 3 sets of each exercise will be performed with all sets performed to voluntary muscular failure, in each session. When multiple sets (weeks 5 onwards) of each exercise are performed, these will be sequentially with 2 min rest between each set.

### Criteria for discontinuing or modifying allocated interventions {11b}

If patients are not able to carry out any of the exercise, then the trainers will work with the patient to develop a suitable alternative exercise.

### Strategies to improve adherence to interventions {11c}

For participants in the home-based group, the trainer will send a message to each participant on the day of their training session to remind them to carry out the exercise and to respond to say they have done it. An exercise log will also be provided for participants.

Those in the gym-based group will be sent a reminder message to ensure attendance at the supervised exercise sessions within our gym facility.

### Relevant concomitant care permitted or prohibited during the trial {11d}

Usual clinical care will be maintained for all patients during the trial.

### Provisions for post-trial care {30}

Usual clinical care will be maintained for all patients following completion of the trial.

### Outcomes {12}

Baseline characteristics will be collected—age, sex, blood pressure, duration of diabetes, current medications, current comorbidities and blood lipids.

All outcomes measures will be assessed at baseline, 16 weeks and 32 weeks in all participants.

#### Primary outcome measure

The primary outcome measure is change in HbA1c from baseline to 32 weeks.

#### Secondary outcome measures

Secondary outcome measures are achieved:
DEXA (GE, Lunar body composition scan) derived whole body and regional lean mass.Functional abilities as assessed by the short performance physical battery test [15].Grip strength (measured 3 times in each hand using a Jamar Dynamometer)One repetition maximum for leg extension and lateral pull down.Number of push-ups (full or on knees) completed.DEXA derived fat mass and distribution.Physical activity levels measured by wrist-worn accelerometer (GENEActiv) for 7 days.Quality of life: EQ-5D-DL questionnaire.Current medications.Blood samples will also be stored for potential measurement of other biomarkers of interest.

#### Optional sub-study

Participants will also have the option to have liver fat measured by MRI and also 5-day continuous glucose monitoring.

#### Qualitative evaluation

A sub-group of participants will be invited for qualitative interviews at weeks 16 and 32 with an equal number of participants (*n* = 15) from each of the home- and gym-based resistance exercise groups. Participants will be invited to take part once they have left or completed the study and semi-structured interviews will take place at the Dasman Diabetes Institute (DDI) in person. All interviews will be audio-recorded and transcribed verbatim, anonymised during transcription and checked for accuracy.

Participants’ experiences and the acceptability of the interventions along with barriers and facilitators will be explored using principles of grounded theory.

### Participant timeline {13}

The schedule of enrolement, interventions and assessments for participants is shown in Fig. 1.

**Fig. 1 Fig1:**
[figure not shown]
Schedule of Enrolement, Interventions and Assessments

### Sample size {14}

Previous research has shown that resistance exercise training can result in an ~ 0.6% decrease in HbA1c [12], with a 0.5% in HbA1c also being classified as a clinically relevant change. To detect a 0.5% decrease in HbA1c (standard deviation within groups 0.79%) in the home-based group or gym group versus control, we would require 40 participants per group at 80% power at the 5% significance level. We will recruit 50 to each group to account for drop out.

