## Assignment of interventions: allocation

### Sequence generation {16a}

Following the baseline assessment, patients will be randomised to the home- or gym-based resistance exercise group or the control group (1:1:1 ratio) using a computer-generated randomisation sequence. Randomisation will be stratified by sex.

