## Statistical methods

### Statistical methods for primary and secondary outcomes {20a}

All statistical analyses will be carried out according to a detailed Statistical Analysis Plan, to be finalised prior to database lock. We will use an intention to treat approach for analysis, using baseline observation carried forward for those who do not attend the 16 weeks visit, and last observation carried forward at the 32 week visit. This will estimate the effect of the interventions. The primary (and secondary) outcomes (all continuous) will be analysed in a hierarchical fashion, first analysing the change in outcome in the gym-based group versus control at 16 weeks at 5% level of significance; this is the group we hypothesise will have the greatest effect size. If this first difference is found to be significant, the home-based group will also be compared to control at the 5% level, and if this is significant, the gym-based group will be compared to the home-based group at the 5% level. The overall type I error will not exceed 5% for each outcome because of the hierarchical nature of the testing. Comparison of the randomised groups at 32 weeks will be conducted in a similar fashion, as a secondary analysis, at the 5% level. As a secondary analysis, we will conduct a per protocol ‘completer’s analyses’ of those who attended at least the 16-week visits (irrespective of their protocol adherence or other characteristics after randomisation). This is a less conservative estimate of the effect of the intervention. Finally, in the per protocol group, we will also investigate the association and correlation of change in HbA1C with change in secondary outcomes.

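### The 80% power is claimed for home as well as gym versus control, but under the fixed testing sequence home has about 68–69% if the two effects are equal

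*Protocol article*

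**What the plan says.** All references are to the protocol article.

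- **Sample size {14}** sets the inputs, "To detect a 0.5% decrease in HbA1c (standard deviation within groups 0.79" percentage points), and concludes that "in the home-based group or gym group versus control, we would require 40 participants per group at 80% power at the 5% significance level". It then adds: "We will recruit 50 to each group to account for drop out".
- **Sequence generation {16a}** allocates to home, gym "or the control group (1:1:1 ratio) using a computer-generated randomisation sequence", so both exercise arms are compared with the same control arm.
- **Statistical methods for primary and secondary outcomes {20a}** puts gym versus control first, as the arm expected to show the larger effect. It continues: "If this first difference is found to be significant, the home-based group will also be compared to control at the 5% level". The same order is used at 16 weeks and again at 32 weeks.
- **Objectives {7}** states the primary hypothesis as "home-based resistance exercise training and gym-based resistance exercise training both reduce HbA1c levels" compared with control.

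The sample size section does not mention the testing sequence.

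**The concern.** The power statement covers home and gym alike, as though each were tested on its own. In the plan, only gym is. Home can be declared effective only in a trial where gym has already won, so its power is the probability that both tests succeed. The primary hypothesis, that both work, is the same event. The 80% therefore describes neither the home comparison as it will be run nor the stated hypothesis.

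This matters because home training is the trial's new question. The background says little is known about unsupervised home training, and the discussion treats the efficacy of resistance training as already established. If home is not declared effective, readers may weigh that result as coming from a comparison with 80% power when it had less.

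**Working it through.** **Inputs from the protocol article.** Difference 0.5 percentage points for either exercise arm; SD 0.79; 40 evaluable and 50 recruited per arm; 5% level; 1:1:1 allocation; gym tested before home. Sidedness is not stated; two-sided is assumed because it reproduces the stated 40 (one-sided would give 31).

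**Step 1. Reproduce the stated figure.**
n per group = 2 × (1.96 + 0.84)² × 0.79² / 0.5² = 39.2, so 40. The t-test version gives 40.2, with power 79.8% at 40. The stated 40 and 80% are confirmed for one comparison.

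**Step 2. Correlation of the two tests.** Each contrast has variance σ²/n + σ²/n, and the two share the control term σ²/n. The correlation is (σ²/n) / (2σ²/n) = 0.5.

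**Step 3. Power for home through the gate, equal effects, 40 per arm.**
- Standard error = 0.79 × √(2/40) = 0.1766.
- Expected test statistic = 0.5 / 0.1766 = 2.83; minus 1.96 = 0.87.
- Single-test power = Φ(0.87) = 80.8% (normal approximation).
- Joint power = P(Z₁ < 0.87 and Z₂ < 0.87) with correlation 0.5 = 69.8%.
- Simulation with t-tests: gym about 80%, home and gym together about 68.5%.

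The gate therefore costs home about 11 to 12 points. The shared control helps a little: independent tests would give 0.808² = 65%.

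**Step 4. Sensitivity.** Joint power, which is the power for home and for both:

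| Scenario | Normal approximation | t-test simulation |
|---|---|---|
| 40 per arm, gym 0.5, home 0.5 | 69.8% | 68.5% |
| 40 per arm, gym 0.6, home 0.5 | 77.3% | 76.1% |
| 50 per arm all observed, 0.5 and 0.5 | 81.1% | 80.1% |
| 50 per arm, 10% at zero change, 0.5 and 0.5 | 74.9% | 74.3% |
| 50 per arm, 20% at zero change, 0.5 and 0.5 | 67.5% | 67.4% |

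The 0.6 for gym is an assumption, borrowed from the roughly 0.6% that the sample size section cites for resistance training; the protocol gives no separate gym effect.

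The last two rows reflect the planned baseline observation carried forward. No dropout rate is stated: 20% is what 40 out of 50 implies, and 10% is shown for range. They assume equal dropout in all arms and no mean change in controls. With a fraction d carried forward, the mean difference is 0.5(1 − d), the control variance is (1 − d) × 0.79², and the exercise-arm variance is (1 − d) × 0.79² + d(1 − d) × 0.5². For d = 0.2 the difference is 0.4, the SDs are 0.707 and 0.734, the standard error is √((0.707² + 0.734²)/50) = 0.144, and single-test power is 79%.

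**The case against.** The strongest reply is that the section gives power per comparison, which is common practice in multi-arm trials, and that it never claims 80% for both arms together. It is true that 40 per group is not an arithmetic error, and a reader who infers one would be wrong. But the sentence names home as one of the comparisons with 80%, and the same article makes that comparison conditional. Per-comparison power is the right description for gym only.

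Second, 68–69% assumes equal effects, whereas the plan expects gym to do better. This stands as a qualification. With gym at 0.6% and home at 0.5%, the gate costs about 4 points (80% to 76%), and the cost shrinks further as the gym effect grows. One should also not attribute every missed home effect to the gate: about one trial in five would miss it with no gate at all.

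Third, 50 per arm are recruited. If all were observed, joint power would be about 80%. The protocol assigns those extra participants to dropout, however, and carrying values forward at zero change brings the figure back to about 75% at 10% and 67% at 20%.

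Two stronger readings are tempting and should be set aside. A larger loss can be produced by setting gym at 0.6% and home at 0.4%, which gives 59%. No document gives a home effect of 0.4%, and at that value home has only 61% power with no gate, so the scenario does not measure the gating loss. A reader might also infer that baseline adjustment would restore 80%. That depends on a baseline-to-follow-up correlation found nowhere in the document, and on whether 0.79% is the SD of change or of level, which the section does not say.

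**Conclusion.** The point holds as a misattributed power statement. On the protocol's own inputs (0.5% in both arms, SD 0.79%, 40 evaluable per arm, shared control, two-sided 5%), power is about 80% for gym versus control and about 68–69% for home versus control, and so for the hypothesis that both work. The home figure rises to about 76% if the gym effect is 0.6%. At 50 per arm with equal effects, it is about 80% if everyone is observed and about 75% down to 67% if 10–20% are carried forward at zero change.

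A reader might infer that the trial is wrongly sized or that the sequence is invalid. The document supports neither: the 40 is correct for the first step, and the fixed ordering is a legitimate way to control type I error within each outcome. What is missing is its cost in power for the second step.

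**What to change.** Reword Sample size {14} so that each figure is tied to the test it describes. For example: with 40 evaluable participants per arm, a difference of 0.5% and an SD of 0.79%, the trial has 80% power for gym versus control, the first step of the fixed sequence. Because home versus control is tested only if that step is significant, power for home versus control, and for showing that both interventions reduce HbA1c, is about 68–69% if the two effects are equal and about 76% if the gym effect is 0.6%.

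The sample size, the testing order and the significance level stay as they are. The cost is wording only, with a less favourable figure for home. Do not cite power under baseline adjustment in this section. Missing data and non-adherence {20c} rules out multivariable models to adjust for confounding, so adopting adjustment would change the analysis and should be argued separately.
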